**Background**

Some normal thyroid tissue is virtually always left behind in the neck following thyroidectomy for differentiated thyroid cancer. This thyroid tissue may or may not contain cancer. Lymph nodes of the neck may also contain metastatic cancer cells that have not been removed at surgery. Radioiodine is therefore usually administered postoperatively to eradicate both normal thyroid tissue and any remaining cancerous tissue.

The activities of radioiodine administered vary markedly in different countries ranging from 1.1 GBq to 7.4 GBq (from 30 to 200 mCi). Such substantial variation in radioiodine activity administered is due to a lack of properly conducted studies in this field. Only three randomized studies have been published, but these studies appear to have methodological shortcomings (Roos et al. 1998). In a small randomized study reported by Johansen et al. 36 patients were treated with radioiodine activity of 1,073 MBq (29 mCi) and 27 patients with 3,700 MBq (100 mCi). Ablation turned out to be equally effective in both groups (58% vs. 52%, respectively), but drawing reliable conclusions from this study is difficult. In another study (Creutzig et al. 1987) radioiodine activities of 1.1 GBq (30 mCi) and 3.7 MBq (100 mCi) were compared in a cohort of 20 patients who did not have metastatic lymph nodes in the neck. No difference in outcome was detected, but the size of the study was again very small. The largest randomized study has been carried out by Bal et al. (1996). In this study the randomization procedure may not have been appropriate, because the patients´ ability to pay for hospital costs influenced randomization, and similarly the radioiodine activity available at the hospital at the time of study entry probably also affected randomization. One hundred and forty-nine patients took part in this trial, and the administered radioiodine activities were 1,110 MBq (30 mCi), 1,850 MBq (50 mCi), 3,700 MBq (100 mCi) or 5,550 MBq (150 mCi). Thyroid ablation was successful in 63% if the cases treated with 1,110 MBq and in 77% of those who received administered activity of 5,550 MBq.

There are thus little data available from randomized studies regarding the optimal dose of administered radioiodine activity needed to ablate the thyroid following thyroidectomy, and the studies carried out thus far appear to have methodological problems. Based on uncontrolled (nonrandomized) studies, the activity required for ablation might depend on the amount of thyroid tissue that is left behind at surgery (Maxon et al. 1992, Malpani et al 1996). This issue, too, is still inadequately addressed in clinical studies.

Radioiodine ablation may be associated with adverse effects, and the frequency and severity of adverse events may be dependant of the activity administered. The most common adverse events include sialadenitis (33%), and temporary taste and smell alterations (27%). Alopecia may occur in up to 28% of the cases. Haematological toxicity may also occur, but severe hematological toxicity is rare. The risk of secondary malignancy appears to be small (de Vathaire et al. 1997). The legislation for radiation protection calls for use of the minimal effective activities in the management of patients.

In sum, the optimal administered activity of radioiodine following thyroidectomy to ablate the thyroid is not known, and further studies are warranted. Unfortunately, research on this issue has been sparse. The best way to obtain reliable information regarding the administered activity is to carry out a prospective randomized clinical trial, where the most commonly used administered radioiodine activities are compared.

**Aims of the study**

The aims of the study are the following:

1. To compare efficacy of two administered activities of radioactive iodine in terms of ablating the thyroid following thyroidectomy. The compared activities will be 1,110 MBq (30 mCi; used e.g. in the United States of America and in France) and 3,700 MBq (100 mCi, the activity usually administered e.g. in Finland).

2. To compare subjective and objective adverse effects between the two groups; and to compare costs related to these treatments (assessed based on the number of days spent in a hospital isolation unit).

3. To evaluate factors that might be predictive for successful ablation, such as the number of metastatic cervical lymph nodes, and the measured absorbed dose at the thyroid bed.

**Study participant inclusion and exclusion criteria**

**The study inclusion criteria are the following**:

1. A total or near total thyroidectomy has been carried out done for either papillary or follicular thyroid cancer.

2. The patient must have read and understood the written informed consent provided prior to study entry. The patient must have signed the informed consent for study participation.

3. The study participant is estimated to tolerate administration of the study treatment (radioactive iodine), and he/she is anticipated to be able to tolerate the stay in an isolation unit.

**The study exclusion criteria are the following:**

1. Pregnancy.

2. Any psychiatric or physical illness that is considered to prevent a stay in a hospital isolation unit for approximately 3 days.

3. Presence of macroscopic cancer in the regional lymph nodes or in the surgical bed that is left behind at surgery; or presence of overt metastases.

**Treatment allocation groups**

The study participants will be randomly allocated to receive either 1,110 MBq (30 mCi) or 3,700 MBq (100 mCi) of radioactive iodine following thyroidectomy.

**Randomisation**

Randomisation is done using a computer program located at the Department of Oncology, Helsinki University Central Hospital. At randomization, patient’s name, the social security number, and the cervical lymph node status (N status) are recorded.

The study participants will be stratified at randomization based on the presence or absence of metastatic cervical lymph nodes at surgery (N+ = macroscopic or microscopic metastases present in the cervical lymph nodes; N0 = no cervical metastases are present).

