**Study power**

We estimate that one radioiodine treatment is successful in 40% of the patients allocated to receive the smaller administered dose (1,100 MBq) and in 60% of the patients allocated to the higher activity (3,700 MBq) group. Using a power (1-) 80%,  0.05 and a one-sided log-rank test, 80 patients need to be recruited to each one of the study arms.

Estimation of patient accrual rate: The number of patients diagnosed with either papillary or follicular thyroid cancer at the Department of Oncology, Helsinki University Central Hospital, and treated with radioiodine after thyroidectomy ranges from 50 to 60 per annum. We estimate that 40 to 50 of these patients may fulfil the inclusion criteria of the study. The duration of the study accrual is estimated to be 3 to 4 years provided that a total of 160 patients are entered to the study.

An interim safety analysis: The study will be discontinued if a difference of 50% or greater will be detected in the proportions of patients whose thyroid is successfully ablated (with no need for retreatment) when one half or the study participants (80 patients) have been treated in the study (p is <0.01).

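### Randomisation is stratified by nodal status, but the only efficacy test the protocol names has no stratum term; naming a stratified comparison of success proportions costs only wording

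*Protocol*

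**What the plan says.** Three places in the protocol bear on this.

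- **Randomisation:** "The study participants will be stratified at randomization based on the presence or absence of metastatic cervical lymph nodes at surgery". Nodal status is recorded at that moment for every patient.
- **Aims of the study, aim 3:** the trial will examine "factors that might be predictive for successful ablation, such as the number of metastatic cervical lymph nodes". No effect size is given, and the factor is offered as a possibility.
- **Study power:** the planning assumption is that "one radioiodine treatment is successful in 40% of the patients allocated to receive the smaller administered dose" and "in 60% of the patients allocated to the higher activity" group. The calculation uses "a one-sided log-rank test, 80 patients need to be recruited to each one of the study arms".

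The protocol has no analysis section. No test or endpoint is labelled primary, and nothing says that the analysis will be unstratified.

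**The concern.** Balancing the arms on a prognostic factor removes that factor's contribution to chance differences between arms. A test that ignores the factor still counts this variation in its standard error, which is then too large for the design. Two consequences follow if nodal status predicts ablation: the true one-sided error rate falls below the nominal 5%, and power is lower than the same patients could give. At stake is a few points of power that cost no patients and no extra data.

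**Working it through.** **1. The plan's own figure.** Inputs from Study power: success 40% and 60%, one-sided alpha 0.05 (z = 1.645), power 80% (z = 0.842). For two proportions with a pooled null variance:

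n per arm = [1.645 × √(2 × 0.5 × 0.5) + 0.842 × √(0.4 × 0.6 + 0.6 × 0.4)]² / 0.2² = (1.163 + 0.583)² / 0.04 ≈ 76.2, so 77.

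Freedman's log-rank formula also gives 77 per arm (hazard ratio ln 0.4 / ln 0.6 = 1.794, half the patients with events). The stated 80 reads as 77 rounded up. Power at 80 per arm without strata is 81.7%.

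**2. Assumptions that the protocol does not supply.** 40% of patients are N+; allocation is exactly balanced within strata; the success gap d between N0 and N+ is the same in both arms; the arm difference is 20 points in each stratum.

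**3. Variances.** With N+ share w = 0.4, w(1 − w) = 0.24, and the between-stratum variance is 0.24d².

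- Null, 50% overall: total 0.25; within strata V0 = 0.25 − 0.24d².
- Alternative, 40% against 60%: within strata V1 = 0.24 − 0.24d².

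**4. Formulas.** The unstratified test uses SE_U = √(2 × 0.25/80) = 0.0791. The stratified test uses SE_S = √(2V0/80). The true spread under the alternative is SE_T = √(2V1/80).

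- Unstratified size = 1 − Φ(1.645 × √(0.25/V0)).
- Power = Φ[(0.20 − 1.645 × SE)/SE_T], with SE = SE_U or SE_S.

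| Gap d | V0 | V1 | SE_S | SE_T | Size, unstratified | Power, unstratified | Power, stratified |
|---|---|---|---|---|---|---|---|
| 0 | 0.2500 | 0.2400 | 0.0791 | 0.0775 | 5.0% | 81.7% | 81.7% |
| 20 points | 0.2404 | 0.2304 | 0.0775 | 0.0759 | 4.7% | 82.2% | 83.0% |
| 30 points | 0.2284 | 0.2184 | 0.0756 | 0.0739 | 4.3% | 82.8% | 84.7% |
| 40 points | 0.2116 | 0.2016 | 0.0727 | 0.0710 | 3.7% | 83.8% | 87.1% |

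**5. Simulation** (80 per arm, 40% N+, balanced within strata; pooled z-test against Mantel-Haenszel).

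- 30-point gap: power 81.9% to 84.4% in one run and 82.4% to 84.6% in another; unstratified size 4.2% and 3.7%.
- 40-point gap: power 83.7% to 87.5% and 83.6% to 87.4%; unstratified size 3.6% and 3.7%.
- 20-point gap: the gain is under 1 point.

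Simulated sizes run slightly below the formula. Taken together, the unstratified size is about 4.5%, 4% and 3.7% at gaps of 20, 30 and 40 points.

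**6. Sensitivity, with the nodal effect as an odds ratio** (N+ share 30% and 50%, 20,000 replicates).

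| Odds ratio for nodal status | Gain in power | Unstratified size |
|---|---|---|
| 1 to 2 | 0 to 0.4 points | 4.5% to 5.0% |
| 3 | 81.7% to 82.9%; 82.5% to 84.1% | 4.3% to 4.4% |
| 5 | 82.8% to 85.9%; 83.2% to 86.9% | 3.5% to 3.7% |

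The stratified test had size 4.5% to 5.1% throughout.

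**The case against.** The strongest objection is that the protocol does not say what the point might be taken to say. The log-rank test stands only in a planning sentence, planning calculations commonly leave out strata, and a log-rank test can itself be stratified. Stratification terms are ordinary content of a statistical analysis plan, and one may exist. This stands: a reader might infer that an unstratified primary analysis has been chosen, but the protocol neither labels a primary test nor rules out strata. The point is therefore conditional on the analysis following the only wording given.

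The gaps of 30 and 40 points are also assumptions. Aim 3 treats nodal burden only as possibly predictive and speaks of the number of nodes, not N0 against N+. Residual macroscopic nodal disease is an exclusion criterion. At an odds ratio of 2 or less the gain is negligible. This stands too.

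The protocol names no blocking or other balancing method. With simple randomisation inside each stratum, the unstratified size at gaps of 20, 30 and 40 points was 5.0%, 5.0% and 5.1%, so the conservatism disappears. The power gain remains, however, and allocation of that kind would in effect not be stratified.

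Finally, the calculations compare proportions rather than use a log-rank test. That matches the planning quantity, which is the proportion successful after one treatment.

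**Conclusion.** The point holds as a recommendation about the choice of analysis. It shows no wrong figure and no contradiction. The forgone power is about 1, 2 and 4 points at assumed gaps of 20, 30 and 40 points with 40% N+, and nothing if nodal status is not prognostic. The mild conservatism further requires balanced allocation within strata, and it errs in the safe direction. The principle is secure; the size is not, because the protocol gives neither the N+ share nor a nodal effect.

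Three stronger readings are not supported.

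- **That planned power is lost.** Every unstratified figure above is over 80%.
- **That leaving out baseline thyroglobulin makes the test conservative.** It is not a stratification factor. At a nodal odds ratio of 3 and 30% N+, the unstratified size is 4.4% without and 4.5% with a strong thyroglobulin effect. Omitting it only forgoes precision.
- **That baseline thyroglobulin and neck uptake go unused.** The section on treatment evaluation and endpoints assesses change in thyroglobulin, and the Day -5 sample is the only pre-treatment value scheduled. Neck uptake enters the absorbed-activity estimate, although the protocol does not say which uptake measurement is meant, and aim 3 examines absorbed dose as a predictor.

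**What to change.** In Study power, name the efficacy comparison as a Mantel-Haenszel test, with a Mantel-Haenszel risk difference and confidence interval, for success after one treatment, stratified by N0/N+ as recorded at randomisation. If an analysis plan already says this, align the protocol sentence with it. The 80 per arm need not change.

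Optionally, add a supporting logistic model with nodal status and log baseline thyroglobulin (Day -5), reported as a standardised risk difference. Its purpose is precision only. In simulations using a linear adjusted model, adjusting for both gained about 2, 4 and 8 points of power at assumed odds ratios per standard deviation of thyroglobulin of 1.5, 2 and 3.

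The cost is wording. Nodal status is already recorded at randomisation and thyroglobulin is already measured. Stratifying carried no penalty when nodal status was not prognostic.

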**Study procedures**

Eligibility to the study will be assessed three to four weeks after surgery by a physician. Concomitant diseases, symptoms and physical status will be assessed. The potential study participants will be informed about the study both orally and in writing. Random allocation between the radioiodine activities [1.1 GBq (30mCi) or 3.7 GBq (100mCi)] may occur after the patient has signed an informed consent.

**Radioiodine administration schedule (please see also institutional guidelines for radioiodine administration)**

**Study Day: Procedure:**

Day -5 (Wednesday) 4 to 5 weeks from surgery The following blood tests will be carried out: serum thyroglobulin, thyroid stimulating hormone, free tri- iodothyronine (T3); blood haemoglobin, white cell count, platelet count; serum Na, K, creatinine, aspartate amino transferase (AST). 7.4 MBq radioiodine is administered orally.

Day -4 (Thursday) Filling of baseline symptom/toxicity questionnaire. Neck radioiodine uptake measurement.

Day 0 (Monday) Radioiodine treatment (either 1,110 or 3,700 MBq, administered as a capsule orally); Geiger counts measured on the neck.

Day +1 and +2 (Tue/Wed) Body Geiger counts measured; discontinuation of isolation allowed when measured total body activity is <15 uSv.

Day +4 (Friday) SPECT and Geiger measurements; filling of adverse event questionnaire; whole body iodine scan

Day +11 (Friday) Neck CT.

Day +14 (Friday) A telephone call to the patient to inform about the results of the scans, filling of the adverse event questionnaire.

Day +90 Hospital visit; includes response evaluation by the physician, filling of the adverse event questionnaire and laboratory tests (serum thyroglobulin, thyroid stimulating hormone, free tri- iodothyronine (T3); blood haemoglobin, white cell count, platelet count; serum Na, K, creatinine, aspartate amino transferase).

**Note**: In case metastatic disease is diagnosed in the whole body iodine scan taken following administration of the ablative dose (this is rare), a supplementary activity of 70 mCi will be administered to the patients who were allocated to receive 1,100 mBq (30 mCi). Patients allocated to the higher activity group (3700 MBq, 100 mCi) will not receive a supplementary dose, but the patients will be evaluated, and repeat radioiodine treatment will be administered if clinically required at approximately 4 months after the date of administration of the first dose.

**Adverse event questionnaire**

A form evaluating adverse effects related to radioiodine treatment (such as neck pain, taste disturbances, and nausea) will be filled before radioiodine treatment, and approximately 5 days, 2 weeks, and 3 months after the date of radioiodine administration. The adverse events will be graded in accordance of the NCI-CTC grading.

**Measurement of absorbed activity in the neck**

The radiation activity absorbed in the neck is estimated using Geiger detector counts, the volume of the target in the neck that accumulates activity as assessed using SPECT imaging, and by calculating the percentage uptake of radioiodine in the neck as compared to the whole body uptake (i.e. neck vs. whole body uptake) using the formula developed by Maxon et al. (1975). The value of information obtained from SPECT as compared with that obtained from conventional whole body imaging will be evaluated when the study has been ongoing for approximately for one year. The activity distribution, including the activities at the medulla, will be estimated by comparing SPECT imaging results with the anatomical information provided by CT images of the neck.

**Treatment evaluation and study endpoints**

Radioiodine ablation will be evaluated from the following points of view: 1) success of ablation and how often radioiodine treatment needs to be repeated to complete ablation 2) change in the serum thyroglobulin levels 3) adverse events of treatment (as assessed with questionnaires and blood tests) 4) as times of disease-free survival and overall survival, and 5) duration of stay in a hospital isolation unit.

Radioiodine treatment is deemed unsuccessful and needs to be repeated whenever

1) abnormal uptake (compatible with presence of thyroid tissue or cancerous tissue) is present in a diagnostic whole body 131I scan carried out with 185 MBq (5 mCi) activity after a minimum of 4 months following radioiodine administration, and a after a minimum of 4-week interruption of thyroxin administration

2) detectable (1 ng/mL or higher) levels of thyroglobulin are present in the serum 4 months or later from the date of administration; includes serum thyroglobulin levels measured under thyroid stimulating hormone (TSH) stimulation (achieved by interruption of thyroxine administration for a minimum of 4 weeks).

3) or palpable neck metastases are detected.

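### Ablation success depends in part on a qualitative reading of the diagnostic scan, and the protocol does not mask that reading to the allocated activity

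*Protocol*

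**What the plan says.** The protocol's Treatment evaluation and study endpoints section lists first "success of ablation and how often radioiodine treatment needs to be repeated to complete ablation". It then gives the failure rule: "Radioiodine treatment is deemed unsuccessful and needs to be repeated whenever" any one of three findings is present.

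- **Scan:** "abnormal uptake (compatible with presence of thyroid tissue or cancerous tissue) is present in a diagnostic whole body 131I scan". The scan is made with 185 MBq, at least 4 months after treatment.
- **Thyroglobulin:** "detectable (1 ng/mL or higher) levels of thyroglobulin are present in the serum 4 months or later from the date of administration".
- **Palpation:** "or palpable neck metastases are detected".

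The scan criterion gives no uptake cut-off, names no reader and does not say what the reader may know. No section of the protocol mentions masking of the patient, the physician or the scan reader.

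Two sections require the treating team to know the arm. The note to the Radioiodine administration schedule sets different management by arm if the post-treatment scan shows metastatic disease. Repeat treatment ties the activity of a repeat ablation to that of the first.

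Study power assumes that "one radioiodine treatment is successful in 40% of the patients allocated to receive the smaller administered dose" and "in 60% of the patients allocated to the higher activity (3,700 MBq) group". It plans 80 patients per arm with a one-sided test at 0.05 and 80% power. The interim rule in the same section compares the proportions successfully ablated.

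**The concern.** A patient is a success only if, among other things, someone reads the diagnostic scan as free of abnormal uptake. On a faint or ambiguous image that is a matter of opinion. The plan allows the opinion to be formed with the allocated activity in view.

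The protocol offers grounds for expectation in both directions. Study power expects the lower activity to do worse. The Background reports two small trials without a difference and notes that radiation protection law favours the smallest effective activity. A reader who leans the first way can create a difference; one who leans the second way can hide one.

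The same classification feeds the final comparison and the interim rule. The exposure is also avoidable, because the diagnostic scan uses the same 185 MBq in both arms and that activity does not itself reveal the allocation. Who reads the scan, and with what information, is trial conduct. It has to be settled before scans are read, and a later analysis plan cannot supply it.

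**Working it through.** **Inputs from the protocol (Study power).** Success 40% (lower activity) and 60% (higher activity); 80 patients per arm; alpha 0.05 one-sided, z = 1.645; power 80%, z = 0.8416. The misreading rate is not given and is assumed below.

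**Step 1: reproduce the plan's figure.** With pooled variance under the null hypothesis,

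n per arm = [1.645·√(2·0.5·0.5) + 0.8416·√(0.24 + 0.24)]² / 0.20² = (1.1632 + 0.5831)² / 0.04 = 76.2, so 77.

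The protocol names a log-rank test. With hazard ratio ln 0.6 / ln 0.4 = 0.557, Freedman's formula gives 77 events, which is 77 per arm at an average event rate of 50%. The stated 80 is consistent with 77 rounded up. Power at 80 per arm is

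Φ[(0.20 − 1.645·√(0.50/80)) / √(0.48/80)] = Φ[(0.20 − 0.1300) / 0.0775] = Φ(0.903) = 81.7%.

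**Step 2: who can be affected.** A patient with thyroglobulin of 1 ng/mL or higher, or with palpable neck metastases, is a failure whatever the scan shows. The reading matters only for the rest, and the protocol does not give their share. It does include every patient expected to succeed: 0.40 × 80 = 32 and 0.60 × 80 = 48, or 80 of 160. Each of these would become a failure if the scan were called abnormal.

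**Step 3: size of the shift.** Let e be the share of patients whose outcome hangs on an equivocal scan, and d the difference between arms in the probability that such a scan is called abnormal. The net shift is b = e × d. For example, e = 10% with d = 0.25, 0.5 or 1 gives b = 2.5, 5 or 10 points. These values are assumptions.

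**Step 4: effect on the test.** With observed success p1 (lower activity) and p2 (higher activity), and m their mean,

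P(reject) = Φ{[(p2 − p1) − 1.645·√(2m(1−m)/80)] / √([p1(1−p1) + p2(1−p2)]/80)}.

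Case A: no true difference, 50% in both arms, lower-activity scans over-called as failures by b. Case B: true 40% versus 60%, lower-activity scans under-called as failures by b.

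| Net shift b | Patients of 80 | A: p1 vs p2 | A: type I error | B: p1 vs p2 | B: power |
|---|---|---|---|---|---|
| 0 | 0 | 50% vs 50% | 5.0% | 40% vs 60% | 81.7% |
| 2.5 points | 2 | 47.5% vs 50% | 9.2% | 42.5% vs 60% | 71.8% |
| 5 points | 4 | 45% vs 50% | 15.6% | 45% vs 60% | 60.2% |
| 10 points | 8 | 40% vs 50% | 35.4% | 50% vs 60% | 35.4% |

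Worked line for A at 5 points: Φ[(0.05 − 1.645 × 0.07896) / 0.07886] = Φ(−1.013) = 15.6%.

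Worked line for B at 5 points: Φ[(0.15 − 1.645 × 0.07896) / 0.07806] = Φ(0.258) = 60.2%.

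**Step 5: effect of the fix.** Masking the reading changes neither the sample size nor the first row of the table.

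**The case against.** The best counter-argument is that the protocol does not show a biased reading and that other criteria limit what a reader can do. Four stronger readings are tempting, and the protocol does not support them.

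- **That the scan alone decides the endpoint.** It is one of three sufficient criteria, and one of the others is a numeric laboratory threshold. If, as an illustration, half the patients with equivocal scans already failed on thyroglobulin, the shift would halve, and 5 and 10 points would become 2.5 and 5. This stands and limits the bias. The limit is loose, however, because every expected success still depends on a normal scan.
- **That the scan is read by a physician who knows the arm.** A reader might infer this from the physician's response evaluation at Day +90. That visit comes before the earliest permitted diagnostic scan, at 4 months, and no such scan is listed for it. The protocol is silent on who reads the scan; it does not specify an unmasked reading. Silence still permits one.
- **That type I error is 16% or 35%.** Those figures need an assumed misreading rate and a direction against the lower activity. The opposite direction costs power instead. They illustrate a possible size and do not demonstrate an effect.
- **That masking costs nothing and needs only a changed request form.** The protocol describes neither a reader nor a form. The Day +4 whole body and SPECT images follow the allocated activity and could reveal the arm, so withholding the activity on paper may not be enough.

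Two smaller points also stand. The protocol never labels a primary endpoint; ablation success has that role by use. Palpation is a judgement too, and is equally unmasked.

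**Conclusion.** The point holds in a limited form. The protocol makes a qualitative scan reading sufficient for failure on the endpoint behind its sample size and interim rule. It requires the treating team to know the arm and does not provide for a masked reading. It therefore leaves this endpoint open to reader expectation.

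The size is conditional. If net differential misreading reached 2.5 to 10 points (2 to 8 of 80 patients in one arm), type I error could rise from 5% to between about 9% and 35%, or power could fall from about 82% to between 72% and 35%, depending on direction. This rests on assumed misreading rates, on a two-proportion approximation to the named test, and, for type I error, on 50% true success in both arms. The bias can act only where thyroglobulin and palpation have not already settled the outcome. The protocol should be changed on this point, but it does not show that the result would be biased.

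**What to change.** Add to the protocol's Treatment evaluation and study endpoints section:

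- Whoever reads the 185 MBq diagnostic scan does so without knowledge of the allocated activity, and without sight of the Day +4 post-treatment images or of records that show the activity.
- The result is recorded as normal or abnormal before the allocation is disclosed.
- The allocation is then disclosed for management as the protocol already provides.

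A written definition of abnormal uptake, set by the investigators in advance, would further narrow the room for judgement. Where feasible, the palpation finding could also be recorded before the allocation is consulted.

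The change needs no additional patients, visits or reader and alters no treatment rule. It does require someone to keep the Day +4 images and the activity out of the reader's view. The small downside is that the reader has less clinical information until the result is recorded.
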